### Statistical analysis

#### Non-inferiority margin

Earlier research^22^ has defined clinically significant improvement on the main outcome measure to be 3.4 points, which is the basis for our non-inferiority margin of 3 points.

#### Non-inferiority

Change over time will be modelled using mixed-effects linear regression with a random intercept and slope (time). The main outcome POEM will be analysed by the regression on time (baseline to end point), group (digital self-care vs guided care) and the interaction of time and group. We will consider digital care to be non-inferior to therapist guided if the upper bound of the one-sided 95% CI for the time × group interaction (α = 0.05) is within the a priori non-inferiority margin of 3 points on the POEM.^36^ In addition, we will investigate non-inferiority in a sensitivity analysis per-protocol framework with data from patients who will have initiated module 4 or further in either of the study arms. As for interpretation of results, if the two-sided 95% CI does not contain zero, this will be viewed as indicative of superiority of the corresponding treatment. We will estimate Cohen’s d by dividing the time × group coefficient by the pooled observed baseline SD. All primary analyses will be conducted intent to treat. The power calculations allow for 10% missing post-treatment data on the primary outcome at 90% power. If we have more than 10% missing data, we will use multiple imputation before conducting the primary analysis.

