#### Power calculation

Based on data from Hedman-Lagerlöf *et al*
17 and Kern *et al,*
19 we expect an in-group effect of about d=0.85 for both interventions. A consultant statistician performed a power calculation. The required sample size was computed based on boot-strapped (5000 simulations) reruns of weekly measured data obtained in the therapist-guided RCT.^17^ The results indicated that a sample size of 174 would be required for 90% power, α=0.05, given a non-inferiority margin of 3 points on the POEM scale and accounting for 10% missing data.

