#### Randomisation/blinding

Participants will be blinded to condition. They will be generally informed that they will be randomised to ‘either one of two types of self-help interventions based on CBT’, not knowing any difference between the conditions. After baseline measurements, included participants will be allocated randomly (1:1) to therapist-guided or self-guided treatment in consecutive even-numbered blocks. Randomisation will be based on a true random number service and conducted by a person blinded to the participants, who is not otherwise involved with the study, using a true random number generator (http://www.random.org). It is impossible for the psychologist performing the inclusion assessment to anticipate participant allocation.

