##### Primary outcome measure

POEM^20^ measures the severity of symptoms of AD, which has a range of 0–28. The POEM has excellent psychometric properties and is widely used.^25^ In this study, in order to be conservative, response is operationalised as a POEM score reduction 4 points or more, and the non-inferiority margin is operationalised as 3 points. This is the same as earlier studies of CBT for AD, based on changes from severe eczema. Another evaluation has found smaller changes, around 2.1–2.9 as ‘likely to be beyond measurement error but unlikely to be clinically important’.^26^ Because of this, as we are including participants with mild, moderate and severe eczema, we could possibly have chosen an even smaller margin.

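### The primary model gives each arm its own baseline POEM mean and makes no baseline adjustment, which costs precision and leaves a conditional bias, though the test stays valid overall

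*Protocol article*

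**What the plan says.** The Non-inferiority section fixes both parts of the model. Random part: "Change over time will be modelled using mixed-effects linear regression with a random intercept and slope (time"). Fixed part: "regression on time (baseline to end point), group (digital self-care vs guided care) and the interaction of time and group". Self-care is declared non-inferior if the "upper bound of the one-sided 95% CI" for the interaction lies "within the a priori non-inferiority margin of 3 points on the POEM". Neither a baseline covariate nor a common baseline mean is mentioned there or elsewhere in the article.

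The Randomisation/blinding section gives the order of events: "After baseline measurements, included participants will be allocated randomly (1:1"), in blocks, with no stratification factor stated. The Primary outcome measure section notes that "we are including participants with mild, moderate and severe eczema". Table 1 lists POEM at Screening, Pre, weekly, mid-treatment and post-treatment, so the data needed for adjustment are already collected.

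**The concern.** Because Pre POEM sits in the response vector and the group term is free, the interaction is a difference in change between arms. Randomisation after baseline makes the expected baseline difference zero, and the model does not use that knowledge. Two things follow.

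- **Precision.** With the same mean structure, a model that uses the common baseline has a smaller variance for the contrast.
- **Conditional bias.** The raw baseline difference is subtracted out, but regression to the mean remains and acts in the opposite direction. If self-care starts worse by chance, it appears to improve more. In a non-inferiority trial that is the unhelpful direction.

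Entry spans mild to severe disease, so baseline POEM may vary widely. At stake is how accurately the bound is placed against a 3-point margin.

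**Working it through.** **1. The plan's own figure.** The Power calculation section says "a sample size of 174 would be required for 90% power", one-sided level and margin as above, "accounting for 10% missing data". With true difference 0, n per arm = 2·SD²·(1.645 + 1.282)²/3². No SD is given. SD 6.40 yields 2 × 40.96 × 8.567/9 = 78 per arm; 78/0.9 = 87; total 174. The implied SE is 3/2.927 = 1.025. The 174 came from a bootstrap of an earlier trial's weekly data, so it can be neither confirmed nor faulted.

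**2. Two-visit illustration (not the planned model).** For baseline–week-12 correlation ρ, the change contrast has variance (2/n)·2σ²(1 − ρ) and the adjusted contrast (2/n)·σ²(1 − ρ²). The ratio is (1 + ρ)/2. Anchored to SE 1.025:

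| Assumed ρ | Variance ratio | Power |
|---|---|---|
| 0.3 | 0.65 | 97.6% |
| 0.5 | 0.75 | 95.9% |
| 0.7 | 0.85 | 93.7% |

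A baseline imbalance shifts the change contrast by −(1 − ρ) times itself.

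**3. The planned model with weekly data.** Assumed: 13 visits, 78 per arm, intercept variance 28, residual variance 8 (baseline SD √36 = 6), 12-week slope SD s from 5 to 7, intercept–slope correlation r. Time is scaled 0 to 1, so Σ(t − mean)² = 182/144 = 1.264.

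- Planned variance = (2/78)(s² + 8/1.264). For s = 5: (2/78)(31.33) = 0.803, SE 0.896.
- Shift per 1-point observed baseline imbalance = (c − 8 × 0.5/1.264)/36, with c = r·√28·s. For r = −0.5, s = 5: (−13.23 − 3.16)/36 = −0.46. For r = 0: −3.16/36 = −0.09.
- Variance with a common baseline mean was obtained by generalised least squares.

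| r | Variance ratio, common vs separate baseline | Shift per 1 point |
|---|---|---|
| −0.5 | 0.72 | −0.46 to −0.60 |
| −0.3 | 0.87 to 0.88 | −0.31 to −0.40 |
| 0 | 0.99 | −0.09 |

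A second set of assumed variance components gave 0.70 to 0.99.

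**4. How often imbalance arises.** For an assumed baseline SD of 5 to 7 and 87 per arm, the SE of the baseline difference is SD·√(2/87) = 0.76 to 1.06. A difference of at least 1 point in either direction then occurs in about 19% to 35% of randomisations. In the two-visit case (ρ 0.4 to 0.7, true difference exactly 3), the false non-inferiority rate of the change contrast is 5% overall. It is 13% to 18% when self-care starts more than 1 SE worse, and 0.2% to 0.9% when it starts more than 1 SE better. The adjusted contrast stays near 5% in both cases. In the weekly model these departures shrink as r approaches 0.

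**5. Is deleting the group term enough?** The Guided care section introduces exposure in week 4; the Digital self-care section does so in week 2. Suppose both arms fall 5 points by week 12, linearly from those weeks. The true difference is 0. The planned contrast averages 0.00; the linear-time model without the group term averages −0.04 to −0.28, favouring self-care. If self-care instead reaches its full fall at week 7, the values are −0.82 (planned) and −0.92 to −1.49 (group term dropped).

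**6. What categorical time costs.** With complete data, the adjusted week-12 variance is (2/78)(V − C²/36), with V = 36 + 2c + s² and C = 28 + c.

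- r = −0.5, s = 7: (2/78)(47.96 − 2.50) = 1.166 against a planned (2/78)(49 + 6.33) = 1.419, ratio 0.82.
- r = 0, s = 5: (2/78)(61 − 21.78) = 1.006 against 0.803, ratio 1.25.

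So if the trend really is a straight line, part or all of the gain in step 3 is spent on not assuming it.

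**The case against.** The strongest reply is that nothing here is an error. The contrast is unbiased over randomisations, its overall type I error is 5%, and a model that meets its own power target is not faulty because a more efficient one exists. That stands, and it limits the point to efficiency and conditional bias.

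Three stronger readings are tempting and are not supported.

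- A reader might infer that power would rise from 90% to about 96%, or that a 1-point imbalance moves the result by half a point. Both come from the two-visit case at an assumed ρ of 0.5. In the planned weekly model the gain may be as little as 1% of variance and the shift about 0.1 point. The near-zero end does imply that the POEM SD grows from 6 at baseline to about 8 or 9 at week 12, which is less plausible on a 0–28 scale, but the article does not exclude it.
- A reader might infer that baseline imbalance is likely because no stratification is stated. Chance imbalance of a point is possible, not probable, and a condensed article may omit such detail.
- A reader might think the remedy is one deleted term with no downside. Step 5 shows otherwise. Randomisation equalises expected observed baselines, not the intercepts of straight lines fitted to trajectories that curve differently.

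**Conclusion.** The point holds as a matter of efficiency and conditional bias. The planned contrast leaves unused the knowledge that the arms share a baseline mean, and it flatters whichever arm starts worse by chance. For the same mean structure the variance ratio is about 0.7 to 0.99, and the shift is about 0.1 to 0.6 point per 1-point imbalance. These ranges depend on assumed variance components, because the article reports none; the direction does not depend on them as long as intercept and slope are uncorrelated or negatively correlated. It does not follow that the primary test is invalid, that 174 is too few, or that 90% power is wrong. The change is worth making, but the trial does not stand or fall by it.

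**What to change.** Before outcomes are examined by arm, define the primary contrast as the week-12 POEM difference (self-care minus guided care) adjusted for Pre POEM, by one of two forms:

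- model post-baseline POEM with Pre POEM as a covariate and read the group difference at week 12; or
- fit a constrained longitudinal model with one baseline mean for both arms and time as a categorical factor.

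Do not simply remove the group term while time stays linear, and do not enter baseline as both response and covariate. In the first form, too, visits are better treated as categories, since a straight line over post-baseline visits meets the same curvature problem.

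The cost is modest. The contrast is redefined, so the Cohen's d built on the interaction coefficient must be redefined with it. A few more mean parameters are estimated, with the possible loss of precision shown in step 6. No new data are needed. Rerunning the existing bootstrap power calculation under the chosen model would replace the assumed ranges with the team's own figures. Because recruitment has begun, the change should be dated and documented.

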#### Resource utilisation

At the primary endpoint, resource utilisation will be preliminary assessed by measuring therapist time for each treatment condition and compared with a typical salary for a clinical psychologist employed in Stockholm, Sweden.

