#### Hypotheses

##### Primary hypothesis

Digital self-care will be non-inferior to ICBT, according to the predefined non-inferiority margin of three points, as measured by the primary outcome (POEM).

##### Secondary hypothesis 1

Digital self-care will be associated with significantly less staff costs than ICBT, in the form of time spent in hours by a licensed psychologist.

##### Secondary hypothesis 2

Digital self-care will be cost-effective compared with ICBT, assessed at 1-year follow-up.

##### Secondary hypothesis 3

Effects on the outcome will be mediated by the amount of time spent by participants on main treatment components.

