
#### Digital self-care

As with guided care, the aim of CBT for AD is to target behavioural and emotional processes, to improve AD symptoms and increase quality of life. The material is similar to guided care but shortened. Likewise, participants, read information and perform exercises in their everyday life. As with guided care, the main treatment components are mindfulness and exposure with response prevention, with a specific focus on itch. Participants will be able to practice mindfulness with the help of instructions and examples. Because it may be challenging to construct relevant exposure exercises without the help of a therapist, participants will receive detailed instructions and guidance, and get to choose exposure exercises from a long list of examples. They will also be free to create their own relevant exposure situations within the intervention. Digital self-care consists of eight modules. The only active interventions, mindfulness and exposure are introduced weeks 1 and 2, respectively. From weeks 3 to 7, no new interventions are introduced and participants are advised to continue practising the interventions, but there is a new theme of education each week, to act as inspiration for exercises. The last 4 weeks, the participant is merely advised to continue practice. There is no therapist, but the study coordinator monitors the process and may contact inactive participants. Participants will access the same digital platform as the guided condition. Participants work entirely at their own pace. Modules will be unlocked automatically if 1 week has passed, and all material in the previous module has been read. Participants will report if they have done their assignments, but there is no control if they do as they report.

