#### Therapists

Only the guided group will have therapist contact. The self-guided group will be managed by the study coordinator. The therapists are licensed psychologists specialised in CBT. All therapists have experience in working with somatic conditions and in a text-based format. All therapists will participate in an introductory workshop before treating in the study. The project coordinator will supervise the therapists regularly and on-demand.

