##### Secondary outcome measures

Demographical data will be collected on screening. Peak pruritus Numerical Rating Scale^27^ is used to measure itching sensations; Perceived Stress Scale^28^ is used to measure general experience of stress; Patient Health Questionnaire-9^29^ is used to measure depressive symptoms; Dermatological Life Quality Index^30^ is used to measure AD-specific quality of life; Insomnia Severity Index^31^ is used to measure severity of sleep problems and possible insomnia; Client Satisfaction Questionnaire-8^32^ is used to measure how satisfied participants are with the intervention. We will also ask participants to report if they experience adverse events associated with the treatment (AE). In addition to this, we will use the Credibility/Expectancy Scale^33^ to measure credibility. At the end of the intervention, the participants will be asked to estimate the Time spent in the Exercises (ToE). Euro-QOL Five Dimensions (EQ-5D)^34^ will be used to assess quality of life from a health economics perspective. Treatment Inventory of Costs in Psychiatric Patients (TIC-P)^35^ will be used to assess healthcare costs. Participant will also rate their user experience of the interventions with the System Usability Scale.^36^ Resource use is measured by the time in minutes the clinician spends on the different tasks associated with administering the intervention, doing interviews, and giving support, or Time spent on Treating. Therapists will register their time spent throughout the intervention, and not at a specific measurement point.

Outcomes at all scales will be compared with available published results regarding other internet-based interventions for each scale.

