#### Cost-effectiveness

At 1-year follow-up, a cost-effectiveness analysis will be performed from a healthcare system perspective, based on recorded therapist time, as well as from a societal perspective. The incremental cost-effectiveness ratio will be estimated at post-treatment and at follow-up. We will also use the TIC-P to collect economic cost data,^34^ together with the EQ-5D.^35^ The costs will be assessed in Swedish krona and converted into US dollar using 2023 as the reference year. The costs of the self-guided and therapist-guided treatments will be modelled as a function of therapist time using the same healthcare index to determine tariffs for licensed psychologists. According to our hypothesis, there should be a significant difference in treatment costs but there should not be any significant difference in societal costs. We will calculate quality-adjusted life-years using the area under the curve approach,^37^ use regression analyses to analyse costs^38^ and use non-parametric bootstrapping with 5000 iterations, where differences in costs and outcomes will be paired. The incremental cost-effectiveness ratio will be used as a cost-effectiveness estimate.^39^

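### Staff time is defined three different ways, and the coordinator's work in the self-care arm has no clearly stated recorder or cost, so the reported saving may be biased in favour of self-care.

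*Protocol article*

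**What the plan says.** Four parts of the protocol article define or use the staff-time measure.

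- Secondary hypothesis 1 expects lower staff costs for self-care, "in the form of time spent in hours by a licensed psychologist".
- Secondary outcome measures gives the broadest definition: "Resource use is measured by the time in minutes the clinician spends on the different tasks associated with administering the intervention, doing interviews, and giving" (the list ends with support). It then names who records: "Therapists will register their time spent throughout the intervention, and not at a specific measurement point".
- Resource utilisation, for the primary endpoint, narrows this: "resource utilisation will be preliminary assessed by measuring therapist time for each treatment condition", valued at a typical psychologist's salary.
- Cost-effectiveness bases the healthcare perspective on recorded therapist time and adds: "The costs of the self-guided and therapist-guided treatments will be modelled as a function of therapist time".

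The intervention sections describe who does the work. Under Digital self-care: "There is no therapist, but the study coordinator monitors the process and may contact inactive participants". Under Therapists: "Only the guided group will have therapist contact. The self-guided group will be managed by the study coordinator", and, for the guided arm, "The project coordinator will supervise the therapists regularly and on-demand". Differences between study conditions gives self-care two clinician contacts, one before the intervention and one after 8 weeks. It gives guided care two clinician telephone evaluations on top of its continuous text contact.

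**The concern.** The two sections that turn time into money use therapist time as the cost driver for both arms, while the intervention sections say that one arm has no therapist. The staff input specific to self-care is the coordinator's monitoring and contact with inactive participants. No section clearly says that anyone records that input or that it is priced.

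Two results depend on the measure: the staff-cost comparison in secondary hypothesis 1, and the treatment-cost input to the cost-effectiveness analysis in secondary hypothesis 2. A lower staff cost in self-care is expected, because removing the therapist is the contrast under study. The useful result is therefore how large the saving is. If part of the self-care delivery cost is left out, the saving is overstated and the incremental cost-effectiveness ratio inherits the error. The primary non-inferiority analysis of POEM is not affected.

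**Working it through.** The article gives no expected hours, standard deviation or power for secondary hypothesis 1, so there is no figure of the plan's own to reproduce. The check is a comparison of sections, followed by an illustration of scale.

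**What each definition counts in the self-care arm**

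| Section | Staff term | Clinician contacts | Coordinator monitoring and contact |
|---|---|---|---|
| Secondary hypothesis 1 | licensed psychologist | counted if made by a licensed psychologist | counted only if the coordinator is one; not stated |
| Secondary outcome measures | clinician (only therapists named as recording) | counted by definition | unclear: may be administration, but no recorder is named |
| Resource utilisation; Cost-effectiveness | therapist | not counted if read literally | not counted if read literally |

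The same arm therefore gets different values under different sections, and the coordinator's time is not clearly included under any of them.

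The clinician contacts do not settle the matter. Both arms have two, so if they are of similar length they largely cancel in the between-arm difference. The coordinator's work in self-care does not cancel.

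**Scale, for illustration only**

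Inputs:
- Guided care: about 15 minutes per patient-week, a general figure for internet-delivered CBT in the Background and not an estimate for this trial; 12 weeks of treatment.
- Coordinator time in self-care: c = 1 to 5 minutes per patient-week (assumed).
- Coordinator supervision of therapists: s = 1 to 4 minutes per guided patient-week (assumed).
- Clinician contacts taken as equal in the two arms, so left out.

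Guided time = 15 × 12 = 180 minutes per patient. If no coordinator time is recorded, the recorded saving is 180 minutes.

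Saving with coordinator time counted = (15 − c) × 12; overstatement = 180 / that saving − 1.

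- c = 1: 168 minutes; 180/168 − 1 = 7%
- c = 2: 156 minutes; 15%
- c = 3: 144 minutes; 25%
- c = 5: 120 minutes; 180/120 − 1 = 50%

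If supervision in guided care also goes unrecorded, the saving with everything counted is (15 + s − c) × 12.

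- s = 1, c = 5: 132 minutes; 180/132 − 1 = +36%
- s = 4, c = 1: 216 minutes; 180/216 − 1 = −17%

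The saving would vanish only if self-care staff time reached 180 minutes per patient, that is, 15 minutes per week.

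**The case against.** A reader might infer that staff cost in self-care is zero by definition and that secondary hypothesis 1 therefore cannot fail. The documents do not support this. The definition under Secondary outcome measures counts clinician minutes on administration, interviews and support, and self-care has two clinician contacts, so its time is positive under that definition. Secondary hypothesis 1 is worded in psychologist hours, not therapist hours. The Resource utilisation section intends a measurement in each arm, and the Cost-effectiveness section models a cost for self-care as well. On this view, therapist time in those two sections is shorthand for the broader measure.

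The strongest further point comes from the Guided care section, which has the study coordinator offering guidance to the other therapists. That wording suggests that the coordinator is one of them. Since the therapists are licensed psychologists who register their time, the coordinator's minutes might then be logged and priced.

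This makes non-recording uncertain, but it does not repair the rule. The Digital self-care section expressly contrasts the coordinator with a therapist, and no section says that coordinator time is recorded. Even if it is, coordinators both manage self-care and supervise guided-care therapists, and the article does not say how their time is divided between the arms.

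It is also fair that the minutes in the illustration are assumed, and that supervision could reverse the net error. And a condensed article may properly leave logging templates, tariffs by staff category and the sharing-out of workshop time to fuller documents; none of that is part of this point. The point is that the article does state a cost driver, and states it inconsistently with its own description of one arm.

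**Conclusion.** The concern holds as an inconsistency that can bias the size of the staff saving, not as a hypothesis that is bound to succeed. Read literally, the Resource utilisation and Cost-effectiveness sections do not count self-care delivery time. Under the Secondary outcome measures definition that time is positive, but the coordinator's monitoring and contact with inactive participants still has no clearly stated recorder or cost.

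Omitting that time favours self-care, by 7% to 50% of the saving under the assumed 1 to 5 coordinator minutes per week and the Background's 15 minutes per week for guided care. Unlogged supervision in guided care works in the opposite direction; with 1 to 4 minutes per week assumed there, the net error runs from −17% to +36%. These figures show scale and do not estimate the error in this trial. Its actual size and net sign cannot be known unless both kinds of coordinator time are recorded. The point should be corrected because secondary hypotheses 1 and 2 rest on this measure and the remedy is cheap.

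**What to change.** In Secondary hypothesis 1, Resource utilisation and Cost-effectiveness, replace therapist time and licensed-psychologist time with the Secondary outcome measures definition, and state in that definition that it includes therapist, study-coordinator and clinician-caller minutes. Log these minutes by arm in both conditions, and record the coordinator's management of self-care separately from supervision of therapists. Report the between-arm difference in minutes and in cost, each with a 95% CI. For cohorts already treated, reconstruct coordinator time from platform and call logs and mark it as estimated.

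The cost is revised wording and a small logging burden for the coordinator and the clinicians who make the calls. No extra participants are needed. The reported saving may become smaller.
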